### Sample size determination

We have performed sample size calculations for CLBP according to another acupuncture study on the same disease using the same primary outcome measure because no such BVA research has been reported [28]. The expected mean difference and common standard deviation between the two groups are estimated (mean difference = 1.5, SD = 2.73) according to that former acupuncture research [28] on CLBP using the 10-cm VAS as a primary outcome measure. For two arms (control-sham BVA and experimental-BVA), we consider the two-sample *t*-test model. Twenty-seven participants will be required per intervention group to achieve 0.80 power (1-β) at the 0.05 α level after adjusting for a 20% attrition rate.

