### Participants

Patients with non-radicular chronic LBP will be recruited with a target sample size of 54 participants.

Inclusion criteria:

Being between 18 and 65 years of age

Experiencing LBP lasting for at least the previous three months

Scoring ≥4 points on a 10-cm visual analog scale (VAS) for bothersomeness of LBP at the time of screening

Exhibiting no abnormalities on neurological examination (for example, lumbosacral nerve function, deep tendon reflexes, plantar response, voluntary muscle activation and sensory function)

Having non-specific, uncomplicated LBP, that is, International Classification of Diseases-10 codes:

M513 Other specified intervertebral disc degeneration

M545 Low back pain

M548 Other dorsalgia

M549 Dorsalgia, unspecified

S335 Sprain and strain of lumbar spine

S337 Sprain and strain of other and unspecified parts of the lumbar spine and pelvis

S336 Sprain and strain of sacroiliac joint

Agreeing to participate and signing informed consent

Exclusion criteria:

Radicular pain

Serious spinal disorders, including malignancy, vertebral fracture, spinal infection and inflammatory spondylitis

Other chronic diseases that could affect or interfere with the therapeutic outcomes, including cardiovascular disease, diabetic neuropathy, active hepatitis, fibromyalgia, rheumatoid arthritis, dementia and epilepsy

Previous spinal surgery or scheduled procedures during the study

Painful conditions induced by traffic accidents

Chief musculoskeletal pain other than back pain

Conditions where BVA might not be safe, including clotting disorders, administration of an anticoagulant agent, pregnancy and seizure disorders

Documented hypersensitive reactions to previous BVA treatments, bee stings or insect bites

Severe psychiatric or psychological disorders

Current use of corticosteroids, narcotics, muscle relaxants or herbal medicines to treat LBP or any medication considered inappropriate by the investigator

Pending lawsuit or receipt of compensation because of LBP

Refusal to participate in the trial or provide informed consent

Inability to read and write in the Korean language

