### Data analysis

The statistical analysis will be performed in the principle of intention-to-treat analysis and per-protocol analysis. For the intention-to-treat analysis, data will be processed with the last observation carried forward method.

A homogeneity test of the baseline characteristics will be performed on both demographical and clinical data using a two-sample *t*-test for quantitative data and a chi-square test for qualitative data. The two-sample *t*-test will be used for the VAS to evaluate the bothersomeness of LBP at baseline and again at four weeks (primary endpoint) for the comparison of the two groups and to determine differences from baseline. For each outcome variable, an analysis of covariance will be performed on the data to adjust the baseline characteristics. Trends over time and time-by-treatment interactions will be explored using a repeated-measures analysis of variance. A chi-square test or a Fisher’s exact test will be performed to determine the difference between groups and the adverse effects, which will be recorded and described as frequency and percentage. All statistical analyses will be carried out with the Statistical Package for the Social Sciences (SPSS, Inc., Chicago, IL, USA) for Windows version 18.0, and a significance level of 0.05 will be used.

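### The stated inputs require about 67 randomised per group, not 27; at 27 per group the two-sided power for 1.5 cm is about 42–51%, not 80%

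*Protocol article*

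**What the plan says.** The Sample size determination section of the protocol article gives a complete set of inputs. The effect and spread, "mean difference = 1.5, SD = 2.73", come from an earlier acupuncture trial in the same condition. The section calls the SD common to the two groups: "The expected mean difference and common standard deviation between the two groups are estimated". The test model is also named: "For two arms (control-sham BVA and experimental-BVA), we consider the two-sample" t-test. The conclusion is: "Twenty-seven participants will be required per intervention group to achieve 0.80 power", "at the 0.05 α level after adjusting for a 20% attrition rate".

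The total of 54 is repeated in the Abstract and in the Participants section, where patients "will be recruited with a target sample size of 54 participants".

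Sidedness is not stated. The Data analysis section says only that "a significance level of 0.05 will be used". That section names the two-sample t-test for the primary outcome, carries the last observation forward for the intention-to-treat analysis, and adds an analysis of covariance for each outcome.

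**The concern.** A standardised difference of 1.5/2.73, about 0.55, is of moderate size. Detecting it with 80% power normally takes more than 50 patients per group, so 27 with attrition already included looks too few by more than half. Everything needed to check the figure is in one paragraph, so the gap cannot be put down to detail left in a fuller document.

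The number sets the size of the whole trial. If the stated SD is right, the trial is presented as having four chances in five of detecting its target effect, while the actual two-sided chance is about even or lower. The Discussion says the results will determine efficacy. A non-significant result read in the light of the 80% claim would count against bee venom acupuncture more heavily than the design allows.

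**Working it through.** **Inputs** (Sample size determination unless noted)
- Difference δ = 1.5 cm; common SD σ = 2.73 cm
- Two-sample t-test, two arms of 27 (total 54, Participants)
- α = 0.05, sidedness not stated: two-sided taken as the convention, one-sided also tried
- Power 0.80
- Attrition 20%, already included in the 27, so 27 × 0.8 = 21.6 completers per group

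Standardised difference: d = 1.5/2.73 = 0.5495, d² = 0.3019.

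**Step 1. Try to reproduce 27.** The normal-approximation formula per group is n = 2(z_α + z_β)²/d².
- Two-sided: 2(1.960 + 0.842)²/0.3019 = 52.0. The exact noncentral-t solution is 52.97, so 53.
- One-sided: 2(1.645 + 0.842)²/0.3019 = 41.0. The exact solution is 41.65, so 42.

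Attrition is then added, with n/(1 − 0.20) as the usual form:

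| Test | Evaluable per group (t) | n/0.8 | n × 1.2 |
|---|---|---|---|
| Two-sided | 53 | 66.25 → 67 | 63.6 → 64 |
| One-sided | 42 | 52.5 → 53 | 50.4 → 51 |

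No cell gives 27. The two-sided requirement is 67 per group, 134 in total, against the planned 54.

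**Step 2. Power for 1.5 cm at the planned size** (noncentral t)

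| Analysed per group | Two-sided | One-sided |
|---|---|---|
| 21.6 | 42.2% | 55.2% |
| 22 | 42.9% | 55.9% |
| 27 (no loss, or every patient kept by carrying values forward) | 50.9% | 63.6% |

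**Step 3. What the planned size can detect** with 80% two-sided power. The required d is 0.873 at 21.6, 0.865 at 22 and 0.777 at 27 per group. Multiplied by 2.73 these are 2.38, 2.36 and 2.12 cm.

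**Step 4. Precision.** The half-width of the 95% confidence interval is t × 2.73 × √(2/n). It is 1.68 cm at 21.6 per group, wider than the 1.5 cm target, and 1.49 cm at 27, about equal to it.

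**Step 5. Where 27 might come from.** This is conjecture, and the finding does not depend on it.
- Leaving out the factor 2 for two groups and using a one-sided alpha: (1.645 + 0.842)²/0.3019 = 20.5 → 21; 21/0.8 = 26.25 → 27.
- Reading the two-sided requirement of about 53–54 per group as the total for both groups: about 27 each, before any attrition.
- An SD misprinted by one digit. With 1.73, the two-sided formula gives 20.9 → 21; 21/0.8 = 26.25 → 27.

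**The case against.** The strongest reply is that the paragraph proves a mismatch without showing which number is wrong. The difference and SD come from a cited study that is not available here. As the last line of Step 5 shows, an SD of 1.73 returns 27 with an ordinary two-sided test, and power with 22 completers would then be 0.80. Replacing the 80% claim by 42% would in that case put a new error into the protocol. This affects the order of the repair: the inputs must be checked first. It does not rescue the paragraph, which is wrong as printed either way.

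Other replies narrow the shortfall but do not close it.
- *Last observation carried forward keeps dropouts in the test.* With all 27 per group analysed, two-sided power is 51%. The honest statement is therefore a range of 42–51%.
- *Alpha may be one-sided.* Power is then 55–64%, so calling it a coin toss or less holds only for two-sided testing. The result is still well below 80%.
- *The analysis of covariance regains power.* The sample size section does not use it and gives no baseline correlation. Assuming a correlation of 0.5–0.6, power with 27 per group is about 63–70%. Reaching 80% needs a correlation of about 0.71 with all 27, or 0.77–0.78 with 22–21.6 completers.

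It is also fair to say that the article nowhere states that a null result will be read as no effect. The proposed sentence on interpretation is a safeguard that follows from low power. Its absence is not a separate error.

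**Conclusion.** The concern holds: the sample size statement is wrong as written. With the printed inputs, 80% two-sided power needs 53 evaluable and 67 randomised per group, about 2.5 times the planned 27 (67/27 = 2.48). At the planned size, two-sided power for 1.5 cm is about 42% with 20% loss and 51% with everyone analysed. No one-sided reading exceeds 64%.

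These figures assume that δ = 1.5 and σ = 2.73 are printed correctly, that allocation is equal, and that the test is the unadjusted two-sample t-test named in the section. If the SD turns out to be misprinted, the power figures change, but the paragraph still needs correcting.

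**What to change.** 1. Check the difference and SD against the cited acupuncture trial and the original calculation, and correct whichever figure is wrong.
2. If 2.73 stands, rewrite the Sample size determination paragraph. Remove the 0.80 claim and state that alpha is two-sided. Suggested text: *With 27 patients randomised per group, the two-sided 5% two-sample t-test has about 42% power for a difference of 1.5 cm (SD 2.73 cm) if 20% are lost, and about 51% if all are analysed. The difference detectable with 80% power is about 2.4 cm and 2.1 cm respectively. A non-significant result will be interpreted from the confidence interval and not as absence of effect.*
3. For reference, record that the stated inputs would need 53 evaluable, or 67 randomised, per group.

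The cost is one paragraph and a less favourable power statement. The restatement needs no extra patients, and because the Trial status section says recruitment is still under way, it can be made before results are known.

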### Data analysis

The statistical analysis will be performed in the principle of intention-to-treat analysis and per-protocol analysis. For the intention-to-treat analysis, data will be processed with the last observation carried forward method.

A homogeneity test of the baseline characteristics will be performed on both demographical and clinical data using a two-sample *t*-test for quantitative data and a chi-square test for qualitative data. The two-sample *t*-test will be used for the VAS to evaluate the bothersomeness of LBP at baseline and again at four weeks (primary endpoint) for the comparison of the two groups and to determine differences from baseline. For each outcome variable, an analysis of covariance will be performed on the data to adjust the baseline characteristics. Trends over time and time-by-treatment interactions will be explored using a repeated-measures analysis of variance. A chi-square test or a Fisher’s exact test will be performed to determine the difference between groups and the adverse effects, which will be recorded and described as frequency and percentage. All statistical analyses will be carried out with the Statistical Package for the Social Sciences (SPSS, Inc., Chicago, IL, USA) for Windows version 18.0, and a significance level of 0.05 will be used.

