### Data collection

A series of measurements to assess back pain-related dysfunction, pain, quality of life and adverse experiences will be collected at baseline and week 1, 2, 3, 4, 8 and 12. At the screening visit, patients will be asked to fill out a questionnaire regarding their sociodemographic characteristics, including age, gender, marital status, residence, occupation and education level. A medical history will be also taken before their physical check-ups, and these factors will determine their eligibility for our study. Participation in can be ended at any stage if the patient refuses to continue or in the presence of significant clinical deterioration, as determined by the attending KMD researchers. For those participants who will be lost to follow-up and who drop out, intention-to-treat analysis will be applied to the existing data (Table 2).

**Table 2 T2:** Schedule for data collection: outcome measures per visit

**Measures**	**Baseline (Week 0)**	**Week 1**	**Week 2**	**Week 3**	**Week 4**	**Week 8**	**Week 12**
Sociodemographic characteristics	x						
Back pain history	x						
X-ray	x						
Visual analogue scale for bothersomeness of low back pain	x	x	x	x	x	x	x
Visual analogue scale for pain intensity of low back pain	x	x	x	x	x	x	x
Oswestry Disability Index	x	x	x	x	x	x	x
EuroQol-5D	x	x	x	x	x	x	x
Beck's Depression Inventory	x	x	x	x	x	x	x
Adverse experiences^a^		x	x	x	x		x
Credibility test^b^	x			x			

a. Adverse experiences : Any adverse experiences at any visit during treatment sessions and 12 weeks will be monitored. The research team will review all trial protocols, monitor patient safety and investigate any adverse events. b. Credibility test : The credibility of the real and sham treatments will be assessed using the validated Korean version of the credibility test.

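### Last observation carried forward is the only missing-data method named for the intention-to-treat analysis; with 20% attrition planned, it can bias the primary difference in either direction and partly overstate late differences

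*Protocol article*

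**What the plan says.** The Data analysis section of the protocol article names two analyses: "The statistical analysis will be performed in the principle of intention-to-treat analysis and per-protocol analysis". For the first it fixes how missing values are handled: "For the intention-to-treat analysis, data will be processed with the last observation carried forward method". No other method is named. Change over time and the time-by-treatment interaction "will be explored using a repeated-measures analysis of variance"; the article does not say whether this uses filled-in values or completers.

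The Data collection section words the same matter differently. For patients lost or dropping out, "intention-to-treat analysis will be applied to the existing data", with no mention of filling in. It also lets participation end "in the presence of significant clinical deterioration, as determined by the attending KMD researchers". The Withdrawal and dropout section ends participation for, among other reasons, fewer than four of the six sessions completed.

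The Sample size determination section assumes "mean difference = 1.5, SD = 2.73" and arrives at 27 per arm "after adjusting for a 20% attrition rate". The timing of that attrition and its split by arm are not given.

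Treatment lasts three weeks, with volumes of 0.2, 0.4 and 0.8 ml in successive weeks. The VAS is recorded at baseline and weeks 1, 2, 3, 4, 8 and 12. The primary visit is week 3 under Primary outcome measurements but four weeks under Data analysis.

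**The concern.** Carrying the last score forward is right only if scores stay level after a patient leaves. This design gives little reason to expect that. Exposure rises through the treatment weeks, so an effect may still be growing when an early dropout is last seen. Treatment then stops, so an effect may fade during follow-up.

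The plan also generates early losses itself. A patient who stops before the fourth session, at two sessions a week, has not reached the third-week volume. If measurement stops too, a baseline, week-1 or week-2 score stands in as the endpoint.

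At stake is the primary difference, which could be diluted or, if dropout is unequal, shifted either way. The week-8 and week-12 comparisons are also affected, because part of each would be copied from earlier visits. The per-protocol analysis is no safeguard, since it does not address dropout bias.

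**Working it through.** **The plan's own figure.** With a difference of 1.5, SD 2.73, two-sided 0.05 and power 0.80, n per arm = 2 × (1.960 + 0.842)² × 2.73² / 1.5² = 52 (exact *t*: 53). Dividing by 0.8 gives 65 (exact *t*: 67). The stated 27 is not reproduced. That is a separate matter; 27 is used below only as the planned number per arm. The standard error of a difference is then 2.73 × √(2/27) = 0.74 cm.

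**Inputs.** From the article: 1.5 cm, SD 2.73, 20% attrition, 27 per arm, visit weeks. Assumed: mean trajectories, dropout timing and arm split. Within each arm, dropout is taken as unrelated to outcome. Positive values favour bee venom acupuncture (BVA).

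**Week 3, equal dropout.** Let the true difference grow linearly: 0, 0.5, 1.0, 1.5 cm at weeks 0 to 3. With a fraction d lost before week 3, the expected carried-forward difference is (1 − d) × 1.5 + d × (mean difference at the last visit seen).
- d = 20%, all last seen at baseline: 0.8 × 1.5 + 0.2 × 0 = 1.20
- d = 20%, spread evenly over weeks 0, 1 and 2: 1.20 + 0.2 × 0.5 = 1.30
- d = 20%, all last seen at week 2: 1.20 + 0.2 × 1.0 = 1.40
- d = 10%, evenly spread: 1.35 + 0.05 = 1.40
- d = 5%, evenly spread: 1.425 + 0.025 = 1.45

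If the effect follows cumulative volume instead (differences 0, 0.21, 0.64, 1.5), the 20% evenly spread figure is 1.26.

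**Week 3, unequal dropout, true difference 1.5.** Assume linear improvement to 3.0 (BVA) and 1.5 (sham), with dropouts last seen at week 1 (1.0 and 0.5).
- 20% lost in BVA only: (0.8 × 3.0 + 0.2 × 1.0) − 1.5 = 1.10
- 20% lost in sham only: 3.0 − (0.8 × 1.5 + 0.2 × 0.5) = 1.70

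**Week 3, no true effect, 30% lost in BVA and 10% in sham.**
- Both arms improve by 2.0, dropouts last seen at week 1 (0.667): (0.7 × 2.0 + 0.3 × 0.667) − (0.9 × 2.0 + 0.1 × 0.667) = 1.60 − 1.87 = −0.27
- Both improve by 3.0, losses spread evenly (mean carried 1.0): 2.4 − 2.8 = −0.40
- Both improve by only 1.5, losses spread evenly (mean carried 0.5): 1.2 − 1.4 = −0.20

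Swapping the dropout rates reverses each sign.

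**Week 12, 20% per arm last seen at week 3, when the difference was 1.5.**
- True week-12 difference 0.5: 0.8 × 0.5 + 0.2 × 1.5 = 0.70, an excess of 0.20
- True week-12 difference 0: 0.2 × 1.5 = 0.30

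**Simulation** (27 per arm, SD 2.73, assumed within-patient correlation 0.5, 20,000 replicates).
- True 1.5 cm, 20% lost before week 3 in both arms: mean estimate 1.29; power 0.39, against 0.51 without dropout.
- No effect, 3-cm improvement in both arms, 30% versus 10% lost: bias 0.40 cm, type I error about 8%.
- Week 12, no true difference, 20% last seen at weeks 3 to 4: bias 0.26 cm, rejection 6.3%.

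**The case against.** The best case for the plan is that the harm is probably modest. The 20% covers twelve weeks, and only losses before the primary visit affect the primary comparison. With 5 to 10% early loss the shortfall is 0.05 to 0.10 cm, small beside a standard error of 0.74 cm. With equal dropout and a growing effect, the bias works against BVA. Time trends are only to be explored, and the stated aim makes no claim of lasting benefit. All of this stands and limits the size of the point. It does not make carrying forward a sound sole method.

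Four stronger readings are tempting, and the documents do not support them.
- A reader might infer that both extremes apply together. They cannot: the week-3 extremes need the 20% to leave early, the week-12 extremes need them to leave after week 3. If all left after week 1 (carried difference 0.5) and the true week-12 difference were 0.5, there would be no late artefact. A half-and-half split gives 0.8 × 0.5 + 0.1 × 0.5 + 0.1 × 1.5 = 0.60.
- A reader might infer that dropout will differ by arm. The Discussion raises venom reactions only as a threat to blinding, skin-test reactors are excluded, and the deterioration rule applies to both arms. Unequal dropout is plausible but assumed.
- A reader might infer that filled-in values make the planned *t*-test's standard error too small. Each patient contributes one value. In a null simulation with 20% lost after week 1 in both arms, the mean reported standard error was 0.753 against an actual 0.761, with type I error 5.2%. Inflation under unequal dropout comes from bias.
- A reader might infer that the method favours BVA. The direction is not fixed.

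It is also fair to say that a mixed model does not cure dropout driven by unobserved outcomes. It does answer the illustrations above, where dropout depends only on arm and time. Beyond that a sensitivity analysis is needed.

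**Conclusion.** The point holds as a weakness in a method the article itself fixes, not as a detail left to an unseen analysis plan. Carrying forward can bias the primary difference through losses before the primary visit. The bias is toward the null when dropout is equal and the effect is growing, and in either direction when dropout differs by arm, including when there is no effect. If the effect wanes, it can partly overstate weeks 8 and 12.

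The premise is firm; the size is not. Under the assumptions shown, 20% early loss in both arms turns 1.5 cm into about 1.2 to 1.4 cm, and 5 to 10% early loss into about 1.45 to 1.40 cm. With 30% versus 10% early dropout and no effect, the spurious difference is about 0.3 to 0.4 cm for a common improvement of 2 to 3 cm, and less for a smaller one. Week 12 is overstated by at most about 0.2 to 0.3 cm if all 20% leave after week 3. The argument is the same whether the primary visit is week 3 or week 4. The plan should be changed.

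**What to change.** In Data analysis, replace both carrying forward and the repeated-measures analysis of variance by a likelihood-based mixed model for repeated measures. Use all observed VAS scores at weeks 1, 2, 3, 4, 8 and 12, with baseline VAS, treatment, visit and treatment-by-visit. Specify an unstructured covariance and, with only 54 patients, a named simpler structure to fall back on if it does not converge.

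First reconcile the primary visit (third week under Primary outcome measurements, four weeks under Data analysis), then take the primary contrast there. Align the existing-data wording in Data collection with the model.

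Because the model assumes data missing at random, add a delta-adjusted or reference-based sensitivity analysis for possible arm-related dropout. Keep carrying forward at most as a further sensitivity analysis.

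The cost is revised wording and slightly more analysis work. The VAS scores are already scheduled, so no extra visits or patients are needed.

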#### Primary outcome measurements

Bothersomeness from LBP will be assessed using the 10-cm VAS for bothersomeness of LBP [18]. To evaluate the clinical severity and impact on activities of daily life in patients with CLBP, the VAS for bothersomeness is selected as a primary outcome measurement. Using the 10-cm VAS (0, absence of bothersomeness; 10, the worst bothersomeness imaginable), the patient will be asked to report the degree of bothersomeness from LBP within the past week. Bothersomeness of LBP will be measured at every single visit at baseline and 1-, 2-, 3-, 4-, 8- and 12-week follow-ups after beginning treatment. The primary end point is the third week follow-up, which marks the end of the six pharmacopuncture sessions.

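### The plan does not say whether the t-test or the ANCOVA decides the primary outcome; naming a baseline-adjusted ANCOVA would settle this and gain power at no cost

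*Protocol article*

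**What the plan says.** All the analysis statements are in the Data analysis section of the protocol article.

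- Primary outcome: a two-sample t-test "will be used for the VAS to evaluate the bothersomeness of LBP at baseline and again at four weeks (primary endpoint"), used "for the comparison of the two groups and to determine differences from baseline". As a two-sample test, the second use reads most naturally as a comparison of change scores between arms.
- Adjustment: "For each outcome variable, an analysis of covariance will be performed on the data to adjust the baseline characteristics". The primary outcome is therefore included. The covariates are not named.
- Analysis sets: "The statistical analysis will be performed in the principle of intention-to-treat analysis and per-protocol analysis".
- Baseline balance: "A homogeneity test of the baseline characteristics will be performed on both demographical and clinical data".
- Repeated-measures analysis of variance is described as exploratory. One significance level, 0.05, covers everything.

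Primary outcome measurements says "Bothersomeness of LBP will be measured at every single visit at baseline" and at each follow-up, and Table 2 schedules it the same way. Sample size determination uses the two-sample t-test model with "mean difference = 1.5, SD = 2.73".

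**The concern.** Up to three tests of one hypothesis apply to the primary outcome: a t-test on the follow-up score, a t-test on change from baseline, and an ANCOVA. No sentence says which one counts. Two things are at stake.

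The first is precision. The method attached to the primary endpoint is not the most efficient one for data the trial will already hold. In a trial of 54 patients that matters.

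The second is the freedom to choose. If the tests disagree, the text does not settle which result is the trial's answer. The ANCOVA itself is also not fully fixed while its covariates are unnamed.

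**Working it through.** **Inputs.** Difference 1.5 cm, SD 2.73 cm, α 0.05, 27 per arm and 20% attrition come from Sample size determination. Assumptions: two-sided testing (sidedness is not stated); 2.73 is the SD of follow-up scores (the text does not say); baseline/follow-up correlation ρ of 0.3, 0.5 or 0.6 (not given).

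**The plan's own figure.** n per arm = 2(1.960 + 0.842)² × (2.73/1.5)² = 52, or 52/0.8 = 65 after attrition (53 and 67 by noncentral t). The stated 27 is not reproduced. This is a separate error; here it only explains why the starting power is low.

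**Power of the follow-up t-test.** The standard error is 2.73 × √(2/27) = 0.743, so the noncentrality is 1.5/0.743 = 2.02 on 52 df. Power is 51%. With 27 × 0.8 = 21.6 per arm, the standard error is 0.831, the noncentrality 1.81, and power 42%.

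**Power of the ANCOVA.** Residual SD = 2.73 × √(1 − ρ²). Noncentral t with one further degree of freedom spent:

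| ρ | variance removed | residual SD | noncentrality (27 per arm) | power, 27 per arm | power, 21.6 per arm |
|---|---|---|---|---|---|
| t-test | – | 2.73 | 2.02 | 51% | 42% |
| 0.3 | 9% | 2.60 | 2.12 | 55% | 46% |
| 0.5 | 25% | 2.36 | 2.33 | 63% | 53% |
| 0.6 | 36% | 2.18 | 2.52 | 70% | 60% |

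**The change-score t-test.** Its variance relative to the follow-up score is 2(1 − ρ): 1.4, 1.0 and 0.8 at the three correlations. The ANCOVA factors 1 − ρ² are 0.91, 0.75 and 0.64, smaller each time.

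**If 2.73 is instead the SD of change.** ANCOVA then removes (1 − ρ)/2 of the change-score variance: 35%, 25% and 20%. With 27 per arm, power goes from 51% for the change-score test to 69%, 63% and 60%. The gain remains, but it now shrinks as ρ rises.

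**Type I error if any significant result may be claimed.** Simulation of 40,000 null trials, 27 per arm, bivariate normal scores, one visit, two-sided 0.05:

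| ρ | follow-up t-test or ANCOVA | change-score t-test added | ANCOVA alone |
|---|---|---|---|
| 0.3 | 6.3% | 9.0% | 4.8% |
| 0.5 | 7.2% | 9.6% | 4.9% |
| 0.7 | 8.1% | 9.9% | 5.0% |

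The per-protocol set and the open choice of covariates are not in these figures.

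**The case against.** The t-test is the natural primary test: it is the one method attached to the primary endpoint, and the sample size is built on it. In a randomized trial it is valid and holds its level. Preferring ANCOVA is advice on efficiency and corrects no invalid analysis. That stands. It also means the error rates above are conditional: they apply only if any significant result may be claimed. The plan states no such rule, though it does not exclude one.

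The size of the power gain is also uncertain. It rests on an assumed correlation, and the entry requirement of at least 4 on the same scale may lower it. At 0.3 the gain is only about 4 points. The 21.6-per-arm figures are cautious too, because last observation carried forward nominally keeps up to 27 per arm in the intention-to-treat analysis.

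A reader might infer four stronger things that the article does not support:

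- **That the primary analysis discards baseline.** The same sentence also covers differences from baseline, which use it, though less efficiently than ANCOVA.
- **That covariates will be picked from the baseline tests.** The homogeneity tests and the ANCOVA are listed separately, and nothing links them. The text shows only that the covariates are unnamed.
- **That intention-to-treat and per-protocol have equal standing.** Both are named without a ranking, but Data collection applies intention-to-treat to patients who drop out. A condensed article may leave the ranking of sets to the full plan.
- **That a larger error rate applies because two visits are in play.** The primary visit is week 3 in Primary outcome measurements and four weeks in Data analysis. That contradiction is a separate defect and is not counted here.

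**Conclusion.** The point holds as one of efficiency and clarity. The plan puts a valid but less efficient t-test on the primary endpoint, places an ANCOVA with unnamed covariates beside it, and does not say which decides.

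With 27 per arm, adjusting for baseline bothersomeness adds about 4, 12 or 19 percentage points of power at correlations of 0.3, 0.5 or 0.6. This rests on the protocol's difference and SD, on 2.73 being the follow-up SD, and on correlations the documents do not give. The case for naming one deciding analysis does not depend on the correlation.

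A reader might also infer that ANCOVA rescues the sample size. It does not: with 27 per arm, 80% power would need a correlation of about 0.7 or more. The change should be made, but the text as it stands does not make the trial's test invalid.

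**What to change.** First reconcile Primary outcome measurements and Data analysis on the primary visit (week 3 or four weeks). Then name one primary analysis: the intention-to-treat comparison of bothersomeness VAS at that visit by ANCOVA, with treatment as factor and baseline bothersomeness VAS as the pre-specified covariate, two-sided 0.05. State that the t-tests on follow-up and change scores, and the per-protocol analysis, are supportive. It would also help to say that the homogeneity tests play no part in choosing covariates.

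The cost is a few lines of wording. The baseline score is already scheduled for every patient, no extra patients or visits are needed, and the planned software runs the model. Trial status reports that recruitment is still under way, so the change can be fixed before unblinding. The sample size needs its own correction.
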